### Study population

Patients diagnosed with a nonsurgical lung cancer (corresponding to more than 85% of all cases), having an estimated life expectancy of at least 4 months (to minimally ensure two data collections), and with FC identified by patients as their main caregiver, and who report having a regular FP, are invited to participate to the study by the OPN. FC are eligible independently of their health status. Using a computer-generated randomization list, these dyads are randomly assigned by the research team to either the experimental group (exposed to the intervention) or to the control group (usual care), as shown in Fig. 3. As the study focuses mainly on FC, they can participate even if their relative with cancer decides not to participate or withdraws before the end of the study. There is no blinding in this trial, so participants and the research team know the group allocation.

**Fig. 3 Fig3:**
[figure not shown]
Trial flow diagram

As FC distress is the primary outcome in this study, the sample size was calculated from the mean scores of distress found in a prior study conducted by our team with a similar population of FC of patients with lung cancer (unpublished abstract presented at the 16th World Congress of Psycho-Oncology, Lisbon, Portugal, 23 October 2014). Based on FC distress scores of respectively 13.7 ± 7.0 at the Hospital Anxiety Depression Scale (HADS) (range = 0–42) and of 23 ± 16 at the Psychological Distress Scale used in the Quebec Health Survey (PDSQHS) (range = 0–100), a sample size of 120 FC (60 per group) was calculated. Considering a 5% *α* error, a power of 80% and an anticipated withdrawal rate of 20% (due to patient deterioration or death), this sample size allows to detect a 33% difference in distress scores between the two groups which is considered clinically significant.

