**Methods/design:**

A total of 120 lung cancer patients and their FC are randomly assigned to the experimental group (exposed to intervention, *N* = 60) or to the control group (usual care, *N* = 60). The intervention includes: (1) systematic FC distress screening and problem assessment near their relative’s cancer diagnosis, and every 2 months, (2) privileged contact with an oncology nurse (ON) away from the patient to address FC problems and (3) liaison by the ON with the family physician of FC reporting high distress (thermometer score ≥5/10), or problems relying on FP expertise. In both groups, FC, patient and process-of-care outcomes are measured at baseline and every 3 months, up to 9 months. The primary endpoint is FC distress measured by the Hospital Anxiety and Depression Scale (HADS) and the Psychological Distress Index used in the Quebec Health Survey (PDQHS). Individual interviews with 10 FC and a focus group with the oncology team will be conducted at the study end to further document the effectiveness of the intervention and its impact on quality of life (for FC) and practice organization (for the oncology team).

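### On the printed means and SDs, the claim of 80% power for a 33% difference holds for the HADS but not for the PDSQHS, where an unadjusted comparison at one time point has about 63%

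*Protocol article*

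**What the plan says.** The Abstract (Methods/design) makes both instruments primary: "The primary endpoint is FC distress measured by the Hospital Anxiety and Depression Scale (HADS) and the Psychological Distress Index". Procedures and data collection also lists both under primary outcomes and ranks neither first. (The Abstract's abbreviation for the Quebec scale differs slightly from the PDSQHS used later; I take them to be the same instrument.)

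The sample-size paragraph, in Study population after Fig. 3, takes its inputs from an earlier study of similar caregivers. The HADS figures are "13.7 ± 7.0 at the Hospital Anxiety Depression Scale (HADS) (range = 0–42") and the PDSQHS figures are "of 23 ± 16 at the Psychological Distress Scale used in the Quebec Health Survey (PDSQHS) (range = 0–100"). From these, "a sample size of 120 FC (60 per group) was calculated". The conditions are a 5% alpha with no sidedness given, 80% power, and "an anticipated withdrawal rate of 20% (due to patient deterioration or death"). The conclusion does not separate the instruments: "this sample size allows to detect a 33% difference in distress scores between the two groups which is considered clinically significant".

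The paragraph names no test, time point, baseline adjustment or correlation between visits. The Analysis section plans group comparisons at each data collection and, in addition, mixed models for repeated measures.

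**The concern.** The two instruments differ in relative spread. The SD is 51% of the mean on the HADS (7.0/13.7) and 70% on the PDSQHS (16/23). The same 33% reduction is therefore a smaller standardised effect on the PDSQHS, and one sample size cannot give both the same power. A single 80% statement for the pair should raise doubt about the PDSQHS.

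What is at stake is how a PDSQHS result is read. The protocol calls a 33% difference clinically significant. A reader who trusts the stated power would expect a simple between-group comparison to miss such a difference one time in five. On the printed inputs it would be missed more than one time in three. A non-significant PDSQHS comparison could then be over-read as evidence against a worthwhile effect, and a split between the two instruments could be over-interpreted.

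**Working it through.** **Inputs, all from the sample-size paragraph.** HADS mean 13.7, SD 7.0. PDSQHS mean 23, SD 16. 60 per group with 20% withdrawal, so 60 × 0.8 = 48 evaluable per group. Alpha 5%, target power 80%, difference 33% of the mean.

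**Assumptions, because the text is silent.** Two-sided test, common SD in both groups, unadjusted comparison of two means at one time point.

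**Formulas.** Difference Δ = 0.33 × mean. Standardised effect d = Δ/SD. Standard error = SD × √(2/n). Power comes from the noncentral t distribution with 2n − 2 degrees of freedom and noncentrality Δ/SE. Enrolled = evaluable/0.8.

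**HADS**
- Δ = 0.33 × 13.7 = 4.52; d = 4.52/7.0 = 0.646.
- SE at 48 per group = 7.0 × √(2/48) = 1.429; noncentrality = 4.52/1.429 = 3.16; power = 87.9%.
- 80% power needs 39 evaluable per group; 39/0.8 = 48.75, so 49 enrolled.
- Detectable difference at 48 per group and 80% power: 4.04 points, 4.04/13.7 = 29.5%.

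The stated claim is met with room to spare.

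**PDSQHS**
- Δ = 0.33 × 23 = 7.59; d = 7.59/16 = 0.474.
- SE at 48 per group = 16 × √(2/48) = 3.266; noncentrality = 7.59/3.266 = 2.32; power = 63.3%.
- 80% power needs 71 evaluable per group; 71/0.8 = 88.75, so 89 enrolled (178 in total).
- Detectable difference at 48 per group and 80% power: 9.24 points, 9.24/23 = 40.2%.

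The stated claim is not met.

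**Can the plan's figure be reproduced?** Neither instrument returns 60 per group: the HADS needs 49 enrolled and the PDSQHS 89. For the HADS the surplus does no harm, because enrolling more than needed still satisfies the claim. Only the PDSQHS falls short.

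**Other readings of the unstated choices, PDSQHS**

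| Reading | Power |
|---|---|
| Two-sided, 48 per group, t-test | 63% |
| Same, normal approximation | 64% |
| 33% taken as one third, t-test | 64% |
| Two-sided, no withdrawal (60 per group) | 73% |
| One-sided 5%, 48 per group | 75% |
| One-sided 5%, no withdrawal | 83% |

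The only one of these readings above 80% drops the withdrawal allowance that the same sentence of the protocol states.

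**The case against.** The strongest reply is that 63% belongs to one analysis and not to the trial. The Analysis section plans mixed models for repeated measures, with a baseline and up to three follow-ups. Suppose, as an assumption, that all visits share one correlation r and that the 7.59-point difference is constant over follow-up. The variance of a baseline-adjusted average of k follow-ups is then SD² × [(1 + (k − 1)r)/k − r²]. PDSQHS power with 48 per group becomes:
- one follow-up: 67% at r = 0.3, 76% at r = 0.5, 82% at r = 0.6, crossing 80% near r = 0.57;
- two follow-ups: at least 86% for r from 0.1 to 0.8;
- three follow-ups: at least 93% over the same range;
- three follow-ups without baseline adjustment: 95% at r = 0.1, 80% at r = 0.5, about 70% at r = 0.8.

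This part of the reply stands. A reader might infer that the trial as a whole had little better than a 60% chance of finding a 33% PDSQHS effect; the documents do not support that. Nor does the reply rescue the printed claim. The sample-size text rests on raw means and SDs and gives no correlation. The protocol commits to no time-averaged contrast, and its wording about change over time suggests group-by-time effects, which may have less power. Deaths also reduce the number of follow-ups.

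Two other readings can be tried. If the SD shrank in proportion to the mean in the intervention group, power would be about 77–78%, still short. If 23 were the lower of the two group means, power would be about 93%, but that is strained because 23 comes from an earlier study of similar caregivers.

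It may also be said that an article condenses the full protocol, so an unreported variance assumption may exist. That is possible, and the fix allows for it. The point is not an omission, however: inputs and conclusion are both printed, and for one primary instrument they do not agree.

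**Conclusion.** The point holds as an error in a stated figure. On the printed inputs, the claim of 80% power for a 33% difference is right for the HADS (about 88%, detectable difference about 29.5%) and wrong for the PDSQHS (about 63%, detectable difference about 40%). This rests on an unadjusted two-sided comparison at one time point, a common SD and 48 evaluable per group. The arithmetic is firm. Whether the authors used a variance assumption they did not report cannot be known from the article.

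Two stronger inferences are not supported. One is that overall power is low because both instruments must be positive: the article contains no such rule. The other is that the PDSQHS must lose its primary status: correcting the power statement does not require it, and changing the endpoint hierarchy of a recruiting, unblinded trial is a separate decision with its own costs.

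**What to change.** Keep 120 caregivers and replace the single power statement with one per instrument, naming the test, its sidedness and the time point. For example, with 48 evaluable per group and an unadjusted two-sided 5% t-test:
- HADS: about 88% power for a 33% difference; 80% power for about 29.5%. This is the instrument for which the 80%/33% claim holds.
- PDSQHS: about 63% power for a 33% difference; 80% power for about 40%.

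If the calculation did rely on baseline adjustment or a repeated-measures contrast, state the contrast, the number of follow-ups it uses, the assumed correlation and its source, and the resulting PDSQHS power.

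The cost is a change of wording, with no extra participants and no change to the endpoints. The downside is that the stated PDSQHS power becomes less favourable unless a justified repeated-measures assumption is supplied.

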### Procedures and data collection

At a regular visit of the patient who is most often accompanied by their FC, the OPN briefly explains the study to them and asks permission to transfer their phone number to the study team. Then, a research professional contacts them to present the study more extensively, get their agreement to participate and set an appointment with them to sign the Consent Form and begin the data collection with them. In both groups, the research professional interviews separately patients and FC at baseline and at 3-month intervals, for a maximum of 9 months, or until the patient’s death (maximum of four data collections), thus minimizing missing data (Fig. 3). Validated tools are used to collect all the study outcomes. At baseline, FC respond to basic questions related to their personal and medical characteristics. They also complete the following validated questionnaires:Primary outcomes:
*Distress* measured by two instruments: (1.1) the HADS [33, 34], a 14-item instrument specifically designed to evaluate distress, anxiety and depression. For each item, the scale varies from 0 (most of the time) to 3 (never). Using the standard criteria suggested by authors of this instrument, distress scores are converted into two categories (absence/presence of distress) while anxiety and depression scores are converted into three (absence/suspected/significant anxiety or depression); (1.2) the global score of the abbreviated version of the PDSQHS [35, 36]. This14-item instrument was derived from the Psychiatric Symptoms Index [37] and has been used in the Quebec general population to estimate the prevalence of clinically significant distress (scores ≥80th percentile), so it permits the comparison of proportions of FC with high distress levels to the ones found in the general population. The PDSQHS scale varies from 1 (never) to 4 (very often).
Secondary outcomes:
*Needs*. The Home Caregiver Need Survey [38] is a 25-item tool covering four categories of needs (informational, practical, emotional and spiritual). FC indicate, for each need, its perceived importance, on a 0 (not important) to 4 (extremely important) scale, and how well it is satisfied (0 = unsatisfied to 4 = completely satisfied).
*Psychological burden*. The French version of the Caregiver Burden Scale in End of Life Care (CBS-EOLC) [39] is a 16-item instrument validated among FC who assist cancer patients in palliative phase. Items vary from 1 (never) to 4 (very often).
*Preparedness for caregiving*. The Preparedness for Caregiving Scale [40] measures the perceived readiness for multiple domains of the caregiving role (providing physical care, emotional support, setting up in-home support services and dealing with the stress of caregiving). This eight-item instrument uses a 0 (not at all prepared) to 4 (very well prepared) scale.
*Quality of Life*. The City of Hope-QoL Scale-Family Version [41] is a 37-item instrument measuring four QoL domains (physical, psychological, social and spiritual), with questions using a 0–10 scale.
*Service and health care resource utilization*. FC report the number of visits to their FP and to any other health/psychosocial professional, meetings to support groups, use of community resources (volunteer services, respite, help for housework, etc.), sick leave, and prescription of sleeping pills, anxiolytic or antidepressant medications.

Measures are also taken at similar intervals with FC relatives with lung cancer, since their physical and mental health may influence FC. At baseline, patients respond to basic questions related to their personal and medical characteristics, and their functional status based on the Karnofsky scale [42] which has a well-known correspondence to the Eastern Collaborative Oncology Group (ECOG) scale [43]. As for FC, they complete distress measures (PDSQHS and HADS) every 3 months, a *Healthnnrelated QoL* measure (European Organization for Research and Treatment of Cancer Quality of Life Core 30: EORTC QLQ-C30) [44], and *service and health care resource utilization* (frequency of emergency room (ER) visits, hospitalizations, homecare services or other services from the community health center). Figure 4 shows the schedule of enrollment, interventions and assessments for all participants.

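### The stated HADS item anchors run against distress for any symptom-worded item, and the article describes no reverse-coding for this primary outcome

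*Protocol article*

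**What the plan says.** Procedures and data collection lists the HADS as the first of two primary distress measures and describes it as "a 14-item instrument specifically designed to evaluate distress, anxiety and depression". The response coding follows: "For each item, the scale varies from 0 (most of the time) to 3 (never"). The rule is stated for every item, with no exception and no reverse-coding step.

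The next sentence says how the scores are classified: "Using the standard criteria suggested by authors of this instrument, distress scores are converted into two categories (absence/presence of distress"). Neither the cut-off nor the direction of the HADS total is given. The same section states more generally: "Validated tools are used to collect all the study outcomes".

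The sample-size paragraph under Study population treats the HADS total as a distress score, with a planning value of "13.7 ± 7.0 at the Hospital Anxiety Depression Scale (HADS) (range = 0–42"). It then sizes the trial to detect a 33% difference between the groups.

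**The concern.** If an item asks how often the caregiver has a symptom, the stated anchors give 0 to the person who has it most often and 3 to the person who never has it. A sum of such items falls as distress rises. The anchors suit a distress score only where the item is worded as well-being. To hold for every item they would need all fourteen to be worded that way, and the article does not say so.

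Nothing else in the text corrects the sentence. No HADS direction is stated, and the 0–42 range is the same whichever way the items run.

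What would be at stake is the sign and size of the group difference on a primary outcome, if anyone scored the data from this sentence. The same items also feed caregiver anxiety and depression, the distress classification and the patients' HADS. If the classification is what enters the McNemar comparison of caregiver and patient distress, that analysis would be affected too.

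**Working it through.** **Inputs.** From Procedures and data collection: 14 HADS items, each coded 0–3. From the sample-size paragraph: mean 13.7, range 0–42, target difference 33%.

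**Step 1: reproduce the stated range.** 14 items × 3 = 42, so 0–42 is reproduced. Replacing each item score x by 3 − x gives the same range, so this figure cannot settle the direction.

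**Step 2: the benefit on a correctly directed score.** 0.33 × 13.7 = 4.52. A favourable 33% difference takes 13.7 to 13.7 − 4.52 = 9.18, an experimental-minus-control difference of −4.52.

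**Step 3: the extreme case.** Assume that all 14 items are symptom-worded and that the sentence is applied literally. The recorded total is then 42 minus the distress total:

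- control: 42 − 13.7 = 28.3
- experimental: 42 − 9.18 = 32.82
- recorded difference: 32.82 − 28.3 = +4.52

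The benefit would appear as a harm of the same size.

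**Step 4: mixed wording.** Let k be the number of symptom-worded items. Under the stated rule these are the ones coded against distress. Assume that every item has the same mean (13.7/14) and carries the same share of the effect (4.52/14). Then:

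- recorded control mean = 13.7 × (14 − k)/14 + k × (3 − 13.7/14)
- recorded difference = −4.52 × (14 − 2k)/14

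| k | Recorded control mean | Recorded difference |
|---|---|---|
| 0 | 13.7 | −4.52 |
| 3 | 16.83 | −2.58 |
| 5 | 18.91 | −1.29 |
| 7 | 21.0 | 0 |
| 9 | 23.09 | +1.29 |
| 11 | 25.17 | +2.58 |
| 14 | 28.3 | +4.52 |

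The difference shrinks for k below 7, vanishes at 7 and changes sign above 7. The article does not give the item wording, so k is unknown and no single row can be taken as the answer. Mixed coding would also change the SD of the total. That effect cannot be computed, because the article gives no correlations between items.

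**Step 5: effect of the correction on the planning figures.** With higher meaning more distress, the range stays 0–42, the planning mean stays 13.7 and the target stays 4.52 points. No sample-size, alpha or power figure moves.

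**The case against.** The strongest reply is that the sentence is a loose description of response anchors in a condensed article and not a scoring algorithm. Nothing in the text says that totals are formed by adding these codes without reversal. The article relies on validated tools, cites the instrument's sources and classifies scores by its authors' criteria. The planning mean comes from an earlier study in which the same team had already used the HADS as a distress measure. Correct scoring in practice is therefore plausible. This stands, and it limits the point to a description that needs correcting and a check that needs doing. It does not make the sentence right: it is an affirmative rule for every item of a primary outcome, and not a detail left to a fuller document.

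Two stronger readings are tempting and are not supported.

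- A reader might infer that the HADS endpoint is in fact reversed or scrambled. The article does not show how the data are scored, and the figures above hold only under literal application and an assumed item wording.
- A reader might see a second fault in the other primary instrument, because "The PDSQHS scale varies from 1 (never) to 4 (very often") runs the other way and its planning score is "23 ± 16 at the Psychological Distress Scale used in the Quebec Health Survey (PDSQHS) (range = 0–100"). Neither is an error. The two instruments are listed separately and no combined score is defined. A 1–4 response scale is compatible with a 0–100 global score. The 33% target directly follows the 0–100 figure, and a conversion formula is something an article may leave to its cited sources.

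**Conclusion.** The HADS coding sentence is wrong as written for any symptom-worded item of a total that the article uses as a distress score, and no reverse-coding step rescues it. Its possible consequence ranges from no distortion (k = 0) to a full change of sign (k = 14, −4.52 becoming +4.52). That range assumes literal application and equal item effects. What is established is a misdescription of a primary outcome that should be corrected. A wrong result has not been established, and the planning figures are unaffected.

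**What to change.** Replace the HADS coding sentence with a statement along these lines: each item is scored from 0 to 3, with 3 denoting the most distress, according to the instrument's published scoring key; items are reverse-coded where that key requires it; the total runs from 0 to 42, and higher values mean more distress.

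Then check the coding of caregiver and patient HADS data already entered against that key. The article reports that the trial is recruiting, so the check is best done now, before any group comparison is run.

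The cost is one or two sentences and a database check. Participants, procedures and sample size are not affected.

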**Fig. 4 Fig4:**
[figure not shown]
Schedule of enrollment, interventions and assessments. FC: family caregiver, Pts: patients

To monitor the administration of the intervention, additional information is collected with FC from the experimental group reporting high distress at screening: the communication with FP, strategies put in place and references to specific resources, as well as the number of FC visits or phone contacts.

In order to promote participant retention, data collections are usually scheduled on the day of a patient regular visit to the oncology clinic. If no visit is planned at the time of a data collection, the questionnaires are mailed to the participants and they are contacted by phone to determine the most convenient way to complete them (either by themselves or with the research professional who may go to their home or complete the questionnaires with them over the phone).

Data from the questionnaires are coded in two separate files and secured in a computer with a passcode. The computer is located in a locked room accessed only by the research team. A SPIRIT Checklist of all items recommended in a randomized controlled trial is included in Additional file 1.

Finally, individual interviews will be conducted with a subgroup of FC in the experimental group at the end of the study (*N* = 10 or until saturation) to document their perception of the intervention usefulness and effect on their QoL. Also, a focus group will be conducted with the OPN and others professionals of the IUCPQ OT, to assess their perception of the usefulness of the intervention and its effect on their practice and organization of care.

